### Intervention and data collection

2.6

Patients enrolled in the registry will undergo implantation of the designated Gore device through standard endovascular techniques, with procedural details recorded in an electronic case report form. The EXCC/IBE module focuses on the endovascular repair of abdominal and iliac aneurysms, with the EXCC device indicated for abdominal aortic aneurysms (AAA) and the IBE device designed for iliac aneurysm repair, including both unilateral and bilateral applications. The CTAG-AC module evaluates the performance of the device in the context of thoracic endovascular aortic repair (TEVAR), while the TBE module examines its use in zone 0∼2 coverage for aortic disease requiring preservation of supra-aortic trunk vessel perfusion. Procedural adjuncts, including additional stent grafts, cervical debranching, and embolization techniques, are employed at the discretion of the treating physician and recorded as part of the intervention data.

Data collection utilizes a validated electronic data capture platform (Medidata Rave®), ensuring consistency across participating sites. Imaging assessments, including computed tomography angiography (CTA), are encouraged, with clinical centers submitting pre- and post-operative scans for independent evaluation by Gore Imaging Sciences (GIS). GIS follows standardized, pre-defined measurement protocols for the evaluation of imaging endpoints, including endoleak classification and device migration, consistent with established core laboratory practices.

Clinical follow-up is structured to follow standard of care at each facility up to ten years for the EXCC/IBE and CTAG-AC modules. The TBE module follows a modified schedule, with assessments concluding at the two-year mark (Table 3).

**Table 3 T3:** Participant timeline: schedule of enrollment and follow up assessment.^a^

Follow-Up Milestone	EXCC & IBE Module	CTAG-AC Module	TBE Module
Pre-procedure assessment	✓	✓	✓
Post-procedure (discharge)	✓	✓	✓
1 month	✓	✓	✓
6 months	✓	✓	-
1 year	✓	✓	✓
Annual follow-up (years 2−10)	✓	✓	-
Final follow-up	10 years	10 years	2 years

Follow-up is designed to assess device integrity, patient outcomes, and potential complications.

a Follow up visits are determined by treatment teams based on good clinical practice.

Independent oversight is provided by an Observational Safety Monitoring Board (OSMB), which assesses the continuing safety of current patients and those yet to be recruited and the ongoing scientific integrity of the registry. The OSMB will be at specified intervals throughout the study for each individual module. Device-related complications are classified according to standardized criteria and reported in accordance with global regulatory requirements.

### Follow-up and clinical outcomes assessment

2.7

The registry evaluates a range of clinical and device-related outcomes, categorized as primary and secondary measures (Table 4). The primary outcomes of interest include technical deployment success, all-cause and lesion-related mortality, and device-related adverse events such as endoleaks, device migration, loss of branch patency, renal function deterioration, and neurological complications, including stroke, paraplegia, and paraparesis (Table 4). Secondary outcomes are device specific and encompass access-related complications, new-onset renal failure, false lumen remodeling in TEVAR-related registries, and health economic parameters, including hospital length of stay and ICU admission rates, depending on the module. Additionally, the EXCC/IBE module assesses quality of life measures, using the EQ-5D-5L, a validated instrument available in over 150 language versions through the EuroQol Research Foundation, ensuring applicability across the registry's geographically diverse participating centers (10, 11), incidence of erectile dysfunction, and buttock claudication as part of long-term follow-up.

**Table 4 T4:** Primary and secondary outcomes for each module.

Primary Outcomes		
• Deployment Technical Success (index procedure only)^a^ Assessment of the following through all follow-up windows (unless indicated) ○ Mortality (all-cause, lesion-related) ○ Device and Treatment-related Adverse Events (AEs), including: ▪ Lesion rupture (treated area) ▪ Lesion enlargement (treated area) ▪ Endoleaks ▪ Device migration ▪ Loss of aortic/branch patency ▪ New onset renal failure (w/in 30 days of the procedure) ▪ Renal function deterioration ○ Serious Adverse Events (SAEs) ○ AEs with unknown causal relationships ○ Device integrity events (e.g., fracture, kinking, compression) ○ Reintervention		

Secondary Outcomes		
AA Module	TA Module	TB Module
Characterization of remote data collection to supplement follow-up activities (utilization, frequency by time, outcomes, contribution to total follow-up, need for elevation of care) New onset buttock claudication/erectile dysfunction	Access-related complications (index procedure only) Transient Ischemic Attack (TIA) New dissection With/without treatment False lumen status/perfusion/remodeling (dissection pathology)	Access-related complications (index endovascular procedure only) Transient Ischemic Attack (TIA) Life threatening bleed Upper extremity ischemia New dissection With/without treatment False lumen status/perfusion/remodeling (dissection pathology)

a Technical success is defined as successful access, delivery, and accurate deployment of the device to the intended location, and retrieval of the delivery system. The absence of any additional corrective procedure related to the device, procedure, or withdrawal of the delivery system. Events will not include interventions at the access site(s), lumbar drains to address spinal cord ischemia, or additional interventions to address non-treatment areas.

### Minimum enrollment targets

2.8

Minimum enrollment targets for the EXCC/IBE modules were established based on an assumed outcome rate 10%, which is on the scale of expected endoleak (12). A small subset of 20% of all subjects (*n* = 600) represents both possible ad-hoc sub-analysis and a conservative estimate of subjects available at 10 years. With the full anticipated enrollment of 2,000 EXCC subjects, there is 80% power to detect a difference between 8.5% vs. 10% rates. For events with rarity of 1/350, there is greater than 80% probability to observe one or more among a small subset of 600 subjects and six or more events among the full 3,000 subjects. Among the full sample of 3,000 EXCC subjects, and an outcome with rate of 10%, a 95% confidence interval length would be 2.2% and among the reduced population of 600, the 95% confidence interval length would be 5.0%.

For the TA module, enrollment targets were derived assuming an outcome rate of 10%, which is on the scale of expected endoleak for this patient population (13). With respect to the anticipated overall registry of *N* = 1,200 subjects, a small subset of *n* = 120 (10%) represents both a possible *ad hoc* subgroup analysis sample as well as a conservative estimate of subjects available at 10 years. With an enrollment of *N* = 1,200, there is greater than 80% probability to observe one or more of an extremely rare events (1/700) and four or more of a rare event (1/200). This enrollment target supports population proportion estimation with exact confidence interval width of, for example, 3.5% for *P* = 10%, or a maximum of 5.7% for *P* = 50%. For subgroup analyses composed of 10% of the registry (*N* = 120), the exact confidence interval widths would be 11.5% for *P* = 10% and 18.5% for *P* = 50%.

Lastly, for the TB module, the minimum enrollment determination was based on detecting rare events and reasonable confidence interval widths for binomial proportion estimates applied to either the overall population or to subgroups. With an enrollment of *N* = 155, there is greater than 80% probability to observe one or more unusual (1/90) and four or more uncommon events (1/25). This enrollment target supports population proportion estimation with exact confidence interval width of, for example, 6.9% for *P* = 4%, or a maximum of 16.3% for *P* = 50%.

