### Participants and enrollment

2.3

As a real-world registry and collaboration across academic and community centers, enrollment is structured to ensure comprehensive regional representation of diverse patient populations through a multi-site approach, encompassing 96 clinical centers for the EXCC/IBE module, 57centers for the CTAG-AC module, and 26 centers for the TBE module (Table 1). The total number of enrolled patients will vary by module. The EXCC/IBE module targets up to 2,000 patients (1,700 and 300, respectively), the CTAG-AC module aims to enroll 1,200 participants, and the TBE module includes approximately 155 subjects. Follow-up duration is tailored to the characteristics of the devices under investigation. The EXCC/IBE, and CTAG-AC modules follow patients for ten years post-procedure, whereas the TBE module has a follow-up period of two years. The duration of the latter was considered sufficient for assessing mid-term device performance, particularly in the context of evaluating regional variations in device utilization and procedural outcomes. This approach is supported by the existence of separate, ongoing longitudinal data collection efforts designed to capture long-term outcomes (9).

**Table 1 T1:** Together aortic registry enrollment.

Devices	Clinical Sites	Enrollment Target			Total
	Total No. of Sites^a^	North America	EMEA^b^	Asia Pacific^c^	
GORE® EXCLUDER® EXCC module	96	790	505	405	1,700
GORE® EXCLUDER® IBE Module		110	45	145	300
GORE® TAG® Conformable with Active Control Thoracic Stent Graft Module	55	600	300	300	1,200
GORE® TAG® Thoracic Branch Endoprosthesis (TBE) Module	26	–	120	35	155

a This is an approximate number as the site selection process is ongoing.

b Europe, Middle East and Asia region.

c Australia, Japan, New Zealand.

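### The EXCC/IBE power, precision and rare-event figures are computed for 2,000 or 3,000 EXCC subjects and so hold for neither the 1,700 EXCC nor the 300 IBE patients planned

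*Protocol article*

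**What the plan says.** Section 2.8 presents its calculation as the basis for both abdominal devices: "Minimum enrollment targets for the EXCC/IBE modules were established based on an assumed outcome rate 10"%. From there on it names only EXCC. The power statement begins "With the full anticipated enrollment of 2,000 EXCC subjects" and continues "there is 80% power to detect a difference between 8.5% vs. 10% rates". The precision statement begins "Among the full sample of 3,000 EXCC subjects" and gives a 95% interval length of 2.2% at a 10% rate. A subset of 600, described as 20% of all subjects, stands for both a possible subgroup and a conservative count at 10 years. It is given an interval length of 5.0% and a better than 80% chance of at least one 1/350 event. For the full 3,000, the chance of six or more such events is also put above 80%.

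Section 2.3 gives a different composition: "The EXCC/IBE module targets up to 2,000 patients (1,700 and 300, respectively"). Table 1 lists "GORE® EXCLUDER® EXCC module" and "GORE® EXCLUDER® IBE Module" on separate rows, with totals of 1,700 and 300. Section 2.6 separates them clinically, "with the EXCC device indicated for abdominal aortic aneurysms (AAA) and the IBE device designed for iliac aneurysm repair".

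**The concern.** The section claims to support two targets, 1,700 and 300, and uses neither number. Its 2,000 EXCC subjects can only be the module total, which includes 300 patients with a different device for a different lesion. Its 3,000 matches nothing in section 2.3 or Table 1. The subset of 600 is 20% of 3,000.

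Replacing 3,000 with 2,000 throughout would not be enough, because 2,000 is not the sample of either device.

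What is at stake is how far the registry's device-level surveillance can be relied on. A regulator or investigator reading section 2.8 would take 600 as its pessimistic case. For IBE that case cannot occur, since it is larger than full IBE enrollment. The same section gives the TB module, with 155 patients, its own detection and precision figures. IBE has none.

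**Working it through.** **Inputs.** EXCC 1,700 and IBE 300, total 2,000 (section 2.3, Table 1). Rate 10%, contrast 8.5% against 10%, rare event 1/350, and 20% remaining at 10 years (section 2.8). Two-sided testing is the default in section 2.9. Alpha is not stated; 0.05 is assumed.

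**Formulas.**
- Width: exact (Clopper-Pearson) 95% interval with x = 0.10n events.
- At least one rare event: 1 − (349/350)^n. Six or more: binomial upper tail with p = 1/350.
- Power, one sample: Φ{[0.015√n − 1.96√(p0(1−p0))] / √(p1(1−p1))}, with each rate in turn as the null p0.

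**Step 1: reproduce the stated figures.**
- Width at n = 3,000: 2.18 points (stated 2.2%). At n = 600: 4.97 points (stated 5.0%).
- At least one 1/350 event in 600: 82.0%. Six or more in 3,000: 85.6%. Both agree with the stated figures of more than 80%.
- Power at n = 3,000, null 10%: [0.8216 − 0.5880]/0.2789 = 0.838, giving 79.9%. Null 8.5%: [0.8216 − 0.5466]/0.3000 = 0.917, giving 82.0%.
- Power at n = 2,000, the number printed beside it: [0.6708 − 0.5880]/0.2789 = 0.297, giving 61.7%; with the other null, 66.1%. A two-sample test gives 37% with 2,000 per arm.

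The full-sample figures, including the 80% power printed beside 2,000, therefore reproduce at 3,000 and not at 2,000.

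**Step 2: the planned numbers.**

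| | n | Width at 10% (points) | P(≥1 event at 1/350) |
|---|---|---|---|
| Stated, full | 3,000 | 2.2 | – |
| Stated, subset | 600 | 5.0 | 82.0% |
| Module pooled | 2,000 | 2.7 | 99.7% |
| EXCC | 1,700 | 2.9 | 99.2% |
| EXCC, 20% left | 340 | 6.7 | 62.2% |
| IBE | 300 | 7.1 | 57.6% |
| IBE, 20% left | 60 | 16.8 | 15.8% |

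**Step 3: EXCC power at 1,700.** Null 10%: [0.6185 − 0.5880]/0.2789 = 0.109, giving 54.4%. Null 8.5%: [0.6185 − 0.5466]/0.3000 = 0.240, giving 59.5%. Exact binomial tests give 53.9% and 57.6%.

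**Step 4: six or more 1/350 events.** 50.8% at 2,000 and 35.9% at 1,700, against more than 80% stated.

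**Step 5: what 300 IBE patients can detect.** Solve 1 − (1−p)^300 = 0.80: p = 1 − 0.2^(1/300), about 1/187. IBE reaches an 80% chance of at least one event only for events about that common or commoner.

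**The case against.** The strongest reply is that section 2.8 is only a sizing paragraph. It commits to no analysis, and the article elsewhere points towards device-level evaluation. Table 1 keeps the devices on separate rows, section 2.1 speaks of assessing several devices, section 2.7 calls secondary outcomes device specific, and section 2.9 plans benchmarking of device performance. On this view the EXCC label is loose wording, and the 2,000 against 3,000 clash is the larger error, to be repaired in the same edit.

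Much of this stands, and it limits the point. A reader might infer that EXCC and IBE will be reported only as one pooled rate, hiding an IBE problem. No section says so, and how outcomes are tabulated is detail that the full protocol or SAP, neither shown, may settle.

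A reader might also infer that regional comparisons are confounded by device, because Table 1 makes IBE 110/900 = 12% of the module in North America, 45/550 = 8% in EMEA and 145/550 = 26% in Asia Pacific. Those shares matter only if an analysis ignores device and the device rates differ. The one stated regional aim concerns the TBE module, section 2.9 plans regression models that could carry device, and the article gives no IBE rate. With EXCC assumed at 10% and no true regional effect, the crude Asia Pacific minus EMEA gap is −0.9, 0, +0.9 and +1.8 points for IBE rates of 5%, 10%, 15% and 20%. Setting the last of these against the planned 1.5-point contrast would be unsound: it takes one assumed rate, and it compares a gap between two groups of 550 with a difference planned for the whole sample.

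The reply does not rescue the numbers. If the registry is meant to evaluate devices, figures that fit neither device are the wrong ones to print.

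**Conclusion.** Section 2.8 is wrong as written. It says it sets the targets for EXCC and IBE, but its figures belong to a sample of 3,000, or a fifth of it, that the design does not contain.

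For EXCC the loss is moderate in precision (2.9 points instead of 2.2) and substantial in power (about 54% to 59% instead of 80%). For IBE the stated figures are out of reach even at full enrollment: 7.1 points and 58%, against 5.0 points and more than 80% for what the section calls a conservative subset.

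The widths and event probabilities rest on the article's own rates and targets. The power figures also assume alpha 0.05 and a one-sample test, the form that reproduces the stated 80% at 3,000. The figures for 60 IBE patients apply the section's own 20% to IBE, assuming the same retention for both devices.

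The conclusion concerns the stated figures. It does not extend to pooled-only reporting or to confounded regional contrasts, which the article does not establish.

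**What to change.** In section 2.8:

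- Stop calling the combined sample EXCC subjects, and use the module total of 2,000 for any pooled figure: width 2.7 points at 10%, one-sample two-sided power 62% to 66%, and a 51% chance of six or more 1/350 events.
- Add a line for EXCC (1,700): width 2.9 points at 10%; power about 54% to 59% for 8.5% against 10%. State the test and alpha used.
- Add a line for IBE (300): width 7.1 points at 10%; 58% chance of at least one 1/350 event; 80% only for events of about 1/187 or commoner.
- Replace 600 with 20% of the planned numbers: 400 pooled, 340 EXCC, 60 IBE. For IBE this gives a width of 16.8 points and a 16% chance of at least one 1/350 event.

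This changes wording and a few numbers. Enrollment, data collection and follow-up stay as they are. The cost is that the figures, above all those for IBE, look less favourable.

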### Statistical analysis

2.9

As a real-world registry, no statistical hypotheses are specified. By default, statistical testing will test for two-sided differences across arbitrary subgroups to better understand clinical outcomes. All data will be included in their appropriate analysis as intention to treat.

Statistical analyses will employ a combination of descriptive and inferential methodologies to ensure comprehensive evaluation of patient outcomes. Kaplan–Meier survival analyses estimate freedom from mortality, reintervention, and major adverse events over time. Cox proportional hazards models will be used to identify predictors of device failure and clinical complications, while multivariate regression models assess the influence of patient demographics, procedural variables, and anatomical characteristics on long-term outcomes. To provide contextual comparisons, the registry integrates historical data from prior observational studies, allowing for benchmarking of device performance against established clinical standards.

The contrast-enhanced computed tomography (CT) component of this study provides a robust foundation for quantitative imaging analysis and potential future applications of machine learning. Contrast CT offers high spatial and temporal resolution that enables precise assessment of vascular anatomy, device positioning, and procedural outcomes. Beyond its immediate diagnostic and procedural value, the imaging dataset has been structured to support the extraction of radiomic and morphological features that could inform predictive modeling. This framework allows for future implementation of advanced analytical approaches, including machine learning-based image analysis, to identify subtle imaging biomarkers and optimize outcome prediction in endovascular interventions.

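### The 80% power claimed for 8.5% vs 10% at 2,000 EXCC subjects reproduces only at about 3,000; at 2,000 a two-sided 5% one-sample test has about 62% to 66%

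*Protocol article*

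**What the plan says.** Section 2.8 sizes the EXCC/IBE module. The minimum targets "were established based on an assumed outcome rate 10%, which is on the scale of expected endoleak". The power sentence follows: "With the full anticipated enrollment of 2,000 EXCC subjects, there is 80% power to detect a difference between 8.5% vs. 10% rates". It gives no alpha, no test, and no indication of which of the two rates is the reference.

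The neighbouring sentences use a different sample size. A subset of 20% of all subjects is given as n = 600, which is 20% of 3,000. The rare-event sentence refers to "six or more events among the full 3,000 subjects". The interval-length sentence again uses 3,000 EXCC subjects.

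Section 2.3 plans neither 3,000 nor 2,000 EXCC patients: "The EXCC/IBE module targets up to 2,000 patients (1,700 and 300, respectively"). Table 1 agrees, with 1,700 EXCC and 300 IBE.

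Section 2.9 states: "As a real-world registry, no statistical hypotheses are specified". It adds: "By default, statistical testing will test for two-sided differences across arbitrary subgroups". It also plans Cox and other regression models, and benchmarking against historical data, without naming a numerical benchmark.

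**The concern.** The power sentence stands alone on 2,000 in a paragraph otherwise built on 3,000. Power depends on N, so the 80% cannot be right at both sizes. The label is also wrong: 2,000 is EXCC plus IBE together.

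This is the only power statement in the justification for the registry's largest module (2,000 of 3,355 patients). A reader who benchmarks an event rate near 10% would take it that a true rate of 8.5% is missed 20% of the time. If the figure belongs to 3,000, the miss rate at the planned size is much higher, and a non-significant benchmark comparison would be read as better powered than it is.

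**Working it through.** **Inputs.** Rates 8.5% and 10%, N = 2,000 and power 80% come from section 2.8. N = 3,000 comes from the adjacent sentences of 2.8. N = 1,700 EXCC comes from section 2.3 and Table 1. Sidedness is the two-sided default of section 2.9.

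**Assumptions.** Alpha 5% is inferred from the 95% intervals in 2.8. One sample against a fixed rate is assumed because no comparison group is sized. Both are varied below.

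**Formula.** Power = Φ( (|p1 − p0| − 1.96·√(p0(1−p0)/n)) / √(p1(1−p1)/n) ), where p0 is the reference rate and p1 the true rate.

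**Reproducing the stated 80%: n = 3,000, p0 = 10%, p1 = 8.5%.**
- √(0.10×0.90/3000) = 0.005477 and √(0.085×0.915/3000) = 0.005092.
- (0.015 − 1.96×0.005477)/0.005092 = 0.838, so power is 79.9% (exact binomial 79.4%).
- With null 8.5% and true rate 10%, power is 82.0% (exact 81.1%).

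**The same test at n = 2,000.**
- √(0.10×0.90/2000) = 0.006708 and √(0.085×0.915/2000) = 0.006236.
- (0.015 − 1.96×0.006708)/0.006236 = 0.297, so power is 61.7% (exact 61.4%).
- With null 8.5%, power is 66.1% (exact 62.8%).

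| n | Null 10%, true 8.5% | Null 8.5%, true 10% |
|---|---|---|
| 3,000 | 79.9% | 82.0% |
| 2,000 | 61.7% | 66.1% |
| 1,700 | 54.4% | 59.5% |

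**N needed for 80%.** n = ((1.96·√(p0(1−p0)) + 0.842·√(p1(1−p1)))/0.015)² gives 3,009 with null 10% and 2,838 with null 8.5%.

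**Detectable rate at n = 2,000.** Against a fixed 10%, power is 78.5% at a true rate of 8.2% and reaches 80% at about 8.17%.

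**Other readings at n = 2,000.**
- Wald, null-variance, arcsine and exact forms, two-sided 5%, one sample: 61% to 67%.
- One-sided 5%: 73.8% (null 10%) and 76.0% (null 8.5%) by the formula above; 72% to 78% over all forms.
- One-sided 10%: 83% to 87%, above the stated figure.
- Two samples, two-sided 5%: 21% for 1,000 vs 1,000, 37% for 2,000 per group, and 43% to 58% against an external group of 3,000 to 10,000. Reaching 80% takes 5,856 per group.

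**The rest of the paragraph, checked at both sizes.**

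| Statement in 2.8 | At 3,000 | At 2,000 |
|---|---|---|
| 20% of all subjects = 600 | 600 | 400 |
| Above 80% probability of six or more events at 1/350 | 85.6% | 50.8% |
| 95% interval length 2.2% at a 10% rate (exact) | 2.2% | 2.7% |

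Every full-sample figure fits 3,000, including the 80%.

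**The case against.** The strongest counter-argument is that nothing in the registry turns on this number. Section 2.9 specifies no hypotheses, there is no success criterion tied to the figure, and section 2.8 also rests on interval lengths and rare-event counts. That stands. A reader might infer that the registry is underpowered for its primary analysis; the document does not support this, because it defines no primary test.

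A second point is that the 62% depends on a test the article never states. That stands too, so the figure must be given with its conditions. It does not rescue the 80%: no two-sided 5% reading tried at 2,000, one-sample or two-sample, exceeds 67%, and one-sided 5% stops at 78%. A one-sided 10% test overshoots at 2,000. It does come to about 80% at 1,700, but that is not the N in the sentence, and it departs from the two-sided default and the 95% intervals.

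A reader might also conclude that the power figure has no meaning because only subgroup tests are planned. That goes too far. Section 2.9 also plans regression models and benchmarking against historical data, so a comparison with an external rate is foreseeable even though no fixed rate is named. The 1,000 vs 1,000 split is only an illustration, since the subgroups are left arbitrary.

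**Conclusion.** The statement is wrong as written. Under a one-sample, two-sided 5% comparison with a fixed rate, the 80% holds at about 3,000 and not at 2,000, where power is about 62% (null 10%) to 66% (null 8.5%). That overstates power by 14 to 18 percentage points. Under the null-10% form the chance of missing a true 8.5% is about 38% instead of 20%. For the 1,700 EXCC patients alone, power is 54.4% to 59.5%.

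The one-sample design and the 5% level are assumptions. The conclusion that 80% is not reached at 2,000 holds across every 5%-level form tried. The consequence is limited to a wrong sample-size justification.

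It is tempting to infer that 3,000 was the intended enrolment, or that one sentence was updated and the rest left. The pattern is compatible with that, but the document does not say so. Section 2.3, Table 1 and the 3,355 total (1,700 + 300 + 1,200 + 155) all agree on 2,000 for the module.

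**What to change.** The sponsor should first confirm the module's target.

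**If 2,000 is right**, delete the power claim, which is consistent with a registry that states no hypotheses, or restate it with its assumptions. For example: *With 2,000 EXCC/IBE subjects, a one-sample, two-sided 5% comparison with a fixed 10% rate has about 62% power at 8.5% and 80% power at about 8.17%; with 1,700 EXCC subjects, power at 8.5% is about 54%.* Label the 2,000 as EXCC/IBE. Then put the rest of the paragraph on the same N:
- 20% of the module is 400, not 600. At 400, the probability of one or more events at 1/350 is about 68%, and the exact 95% interval length at a 10% rate is about 6.1%.
- The probability of six or more events at 1/350 is about 51%, not above 80%.
- The exact 95% interval length at a 10% rate is about 2.7%, not 2.2%.

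If 600 is kept as a subset, describe it as 30% of 2,000 (600/2,000).

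**If 3,000 is the true target**, correct section 2.3, Table 1 and the 3,355 total, and state whether 3,000 means EXCC alone or EXCC plus IBE.

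The first route costs one paragraph of text and less favourable stated figures, with no extra patients. The second would mean 1,000 more patients than section 2.3 plans if 3,000 covers the whole module, and 1,300 more if it means EXCC alone.

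### The 80% power for 8.5% vs 10% in section 2.8 names no comparison, is not reached at 2,000 subjects (about 62–66% one-sample), and does not apply to the default subgroup tests in section 2.9 (at most about 21%)

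*Protocol article*

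**What the plan says.** Section 2.8 (Minimum enrollment targets) of the protocol article says that the EXCC/IBE targets were "established based on an assumed outcome rate 10%, which is on the scale of expected endoleak". It then makes its one power statement: "With the full anticipated enrollment of 2,000 EXCC subjects", "there is 80% power to detect a difference between 8.5% vs. 10% rates". It does not say whether 10% is a fixed reference or the rate in a second group, and it gives no alpha.

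The same paragraph also works from a larger cohort. It has "A small subset of 20% of all subjects (*n* = 600", which implies 3,000 in total, and it gives an interval length "Among the full sample of 3,000 EXCC subjects". Section 2.3 (Participants and enrollment) says: "The EXCC/IBE module targets up to 2,000 patients (1,700 and 300, respectively". Table 1 agrees with section 2.3.

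Section 2.9 (Statistical analysis) specifies no hypotheses. It then says: "By default, statistical testing will test for two-sided differences across arbitrary subgroups to better understand clinical outcomes". It also plans Cox and multivariable regression models, and says that "the registry integrates historical data from prior observational studies, allowing for benchmarking of device performance against established clinical standards". No test is named for that benchmarking.

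**The concern.** A power figure belongs to a particular test. Section 2.8 prints the figure without the test, and the next section describes, as the default, a test in which each arm holds only part of the cohort. A two-sample comparison needs far more patients than a comparison of the whole cohort with a rate treated as known, so the same 80% cannot serve both.

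Two things are at stake. First, the printed 80% may not be what the module delivers at its own enrolment target, even on the most favourable reasonable reading. Second, a reader going from section 2.8 to section 2.9 could take it as the ability to separate devices, regions or anatomies by 1.5 percentage points, which is far beyond the subgroup tests at this size.

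**Working it through.** **Inputs.** Rates 8.5% and 10%, and stated power 80% (section 2.8). Sample size 2,000 (the power sentence, section 2.3 and Table 1), 3,000 (elsewhere in section 2.8), and the split EXCC 1,700 / IBE 300 (section 2.3, Table 1). Two-sided testing (section 2.9). Assumptions: alpha 0.05, and the subgroup splits 50/50 and 20/80, since the article states neither.

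**Step 1. Reproduce the 80%.** One-sample test of the whole cohort against a fixed rate p0, true rate p1:

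power = Φ{ [ |p1 − p0| − 1.96·√(p0(1−p0)/n) ] / √(p1(1−p1)/n) }

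- n = 3,000, p0 = 10%, p1 = 8.5%: (0.015 − 1.96 × 0.005477) / 0.005092 = 0.838, power **79.9%** (exact binomial 79.4%). The n required for 80% is 3,008.
- n = 2,000, same rates: (0.015 − 1.96 × 0.006708) / 0.006236 = 0.297, power **61.7%**.
- n = 2,000, p0 = 8.5%, p1 = 10%: (0.015 − 1.96 × 0.006236) / 0.006708 = 0.414, power **66.1%**.
- n = 1,700 (EXCC alone): 54.4% or 59.5%, depending on which rate is fixed.

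Other variance choices, the arcsine form and the exact test give 60.9% to 67.2% at 2,000, two-sided. A one-sided 5% test at 2,000 gives 72.3% to 77.7%. None reaches 80%.

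**Step 2. The subgroup test of section 2.9.** Pooled two-sample z test, with p̄ the weighted mean rate:

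power = Φ{ [ |p1 − p2| − 1.96·√(p̄(1−p̄)(1/n1 + 1/n2)) ] / √(p1(1−p1)/n1 + p2(1−p2)/n2) }

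For 1,000 vs 1,000: (0.015 − 1.96 × 0.012957) / 0.012953 = −0.803, power 21.1%.

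| Comparison, 8.5% vs 10% | Power |
|---|---|
| 1,000 vs 1,000 | 21.1% |
| 400 vs 1,600, smaller group at 8.5% | 13.6% |
| 400 vs 1,600, smaller group at 10% | 16.6% |
| EXCC 1,700 vs IBE 300, IBE at 10% | 14.5% |
| EXCC 1,700 vs IBE 300, IBE at 8.5% | 11.2% |
| 1,500 vs 1,500 | 29.4% |
| 2,000 per group | 37.3% |
| 3,000 per group | 51.8% |

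Over all splits the maximum is 21.2% within 2,000 and 29.5% within 3,000. For 80% power about 5,860 patients per group would be needed.

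**Step 3. What a subgroup test can detect with 80% power at 2,000**, one group at 10%:

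- 1,000 vs 1,000: the other group at 6.55% or lower, or 14.08% or higher; about 6.5% or 14.1%.
- 400 vs 1,600, larger group at 10%: the smaller at 5.68% or lower, or 15.07% or higher; about 5.6% or 15.1%, rounded away from 10%.

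**The case against.** The strongest reply is that the two sections do not contradict each other. Section 2.8 attaches the power to full enrolment, not to subgroups, and treats a subset of 600 separately with its own interval length. Section 2.9 sets no hypotheses and calls its subgroups arbitrary; a registry need not be powered for exploratory comparisons. This stands in part: a reader might infer that the article promises 80% power for subgroup tests, and it does not.

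A reader might also infer that subgroup tests are the only ones planned. The text says they are the default, and it adds regression models and benchmarking. A comparison with a fixed rate could serve the benchmarking. But no test is named there, and historical data carry sampling error of their own.

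It is also tempting to say that non-significant subgroup results will be reported as evidence of similar performance. The article plans no such claim.

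Nor does 21% hold whichever way the enrolment numbers are reconciled: at 3,000 the ceiling is 29%.

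What the reply does not remove is the printed figure. Having no hypotheses, or leaving details to an analysis plan, does not excuse a stated power that fails at the sample size in its own sentence. The separate treatment of the subset gives rare-event probability and interval length, not power for a comparison.

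**Conclusion.** The point holds in two parts. First, 80% power does not follow from 2,000 subjects: a one-sample two-sided 5% test gives about 62% (66% with the fixed rate at 8.5%), and 80% needs about 3,000. Second, whichever enrolment number is right, the figure does not apply to the default subgroup tests. Their power for 8.5% vs 10% is at most about 21% within 2,000 and 29% within 3,000. Within 2,000 it is about 14–17% for a 20%/80% split and 11–15% for EXCC vs IBE, depending on which group has the lower rate.

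The second part survives correction of the 2,000/3,000 mismatch. Restoring 3,000 makes the 80% true only for a fixed-rate test that section 2.9 does not name; keeping 2,000 lowers that test's power to about 62%.

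The conclusion rests on alpha 0.05, which the article does not state, and on the assumed splits. That the authors used a one-sample calculation is inferred from the arithmetic; the article does not say so. The inference is strong, since even 3,000 per group reaches only 52% in a two-sample test.

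**What to change.** In section 2.8:

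1. Reconcile 2,000 and 3,000, then restate the power for the number kept (about 62% at 2,000 against a fixed 10%).
2. Name the comparison and alpha behind 8.5% vs 10%, apparently one-sample against a fixed reference rate at two-sided 5%, and say that the figure does not cover the subgroup tests in section 2.9.
3. Add what a two-sided 5% subgroup test can detect with 80% power at 2,000: about 10% vs 6.5% or 14.1% for an even split, and about 10% vs 5.6% or 15.1% for a 20%/80% split.

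In section 2.9, say that subgroup differences will be reported with 95% confidence intervals.

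This costs a few sentences and no extra patients. The downside is a less favourable stated power.
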